## Abstract

**Background:**

Lower urinary tract dysfunction or functional urinary incontinence is a common condition with a prevalence up to 21% between 6 and 8 year-old children. It is associated with an impaired quality of life, lower self-esteem, and social stigmatization. Urotherapy is the first treatment of choice for functional daytime urinary incontinence (DUI) in children. Alarm therapy can be a part of urotherapy as it provides the child adequate feedback on wetting accidents. Current alarm systems notify either at a set interval or give a notification when wetting has already occurred to prompt the child to go to the toilet. These alarms do not teach the child the interpretation of the bladder sensation preceding wetting accidents. A new wearable bladder sensor, the SENS-U, recently became available. This is a relative small, wireless ultrasonic sensor, which continuously monitors bladder filling. The SENS-U is able to provide an alarm at the exact moment voiding is warranted. It facilitates the child to learn the sensation of bladder filling preceding voiding in an easier way, increasing the learning curve throughout treatment. Its additional effect in urotherapy on continence and cost-effectiveness is to be determined.

**Methods/design:**

This is a multi-center clinical superiority parallel-group randomized controlled trial including a total of 480 children. Participants between 6 and 16 years of age with functional DUI in which urotherapy is offered as the next treatment of choice are eligible. Four centers, two academic hospitals, and two general care (peripheral) centers are participating. Participants will be randomized at a 1:1:1 ratio into three groups: urotherapy (care as usual), urotherapy with the SENS-U added for 3 consecutive weeks throughout the training, or urotherapy with a SHAM device for 3 weeks. The primary outcome is number of wetting accidents per week after 3 months of training, compared between the SENS-U and the SHAM device. The magnitude of the placebo effect will be assessed by comparing the results of the SHAM group versus the control (care as usual) group.

**Discussion:**

To our knowledge, this is the first trial studying not only the effect but also the cost-effectiveness of alarm interventions as commonly added in urotherapy.

**Trial registration:**

ISRCTN44345202. Registered on March 2022

**Supplementary Information:**

The online version contains supplementary material available at 10.1186/s13063-022-06600-6.

## Background

Lower urinary tract dysfunction (LUTD; functional incontinence) is a common condition with a prevalence up to 21% in 6–17-year-old children [1, 2]. It is associated with an impaired quality of Life, lower self-esteem, and social stigmatization [3, 4]. Children rate “wetting their pants in class” repeatedly in the top 5 of most stressful life events [5].

According to the International Children’s Continence Society (ICCS), urotherapy is the first treatment of choice for functional urinary incontinence [6]. Urotherapy uses non-pharmacological, non-surgical methods and focuses on behavioral interventions, largely based on cognitive-behavioral psychotherapy. The main aim of urotherapy is to achieve the normalization of the micturition and bowel pattern and to prevent further functional disturbances by repeated training [6]. Studies on the effectiveness of urotherapy report success rates between 40 and 70% [7]. A meta-analytic evaluation of incontinence interventions reported a success rate of urotherapy of approximately 54% within 1 year of treatment (complete dry in 44% and a maximum of one wet episode a week in 10%). The overall reported spontaneous recovery rate in children is 15% per year [7–9].

Additional tools often used in urotherapy are voiding diaries, frequency voiding charts (FVC), uroflowmetry, and alarm interventions [6]. The voiding diary is used as a feedback tool that makes children aware of their voiding behavior. An alarm system gives either feedback when wetting accidents has occurred or notifies the child a set interval to go to the toilet. These systems do not teach the child the interpretation of the bladder sensation that precedes wetting accidents. A new wearable bladder sensor recently became available, the SENS-U. This is a relative small, wireless ultrasonic sensor, which continuously monitors bladder filling and alarms the child when it is time to void. The SENS-U may increase children’s awareness of the sensation of a full bladder. It can be personalized by adjusting the percentage of bladder filling at which it sends an alarm, based on the child’s own bladder capacity and FVC [10–12]. This teaches children which bladder sensation corresponds to a nearly full bladder and when it is time to void.

In current urotherapy, the bladder sensation that corresponds to a full bladder is explained by the urotherapist. Biofeedback on bladder filling with the SENS-U enables children to directly feel what the urotherapist means, thereby inducing less trial-and-error and reducing the number of failing experiences. This could improve urotherapy, as a normally time consuming treatment, with less consultations needed during training and subsequent cost reduction.

Proof-of-concept of the SENS-U and its safety and feasibility have already been established [10–12]. In a pilot study of 15 patients between 6 and 16 years, children responded positively to the notification [12]. Clinical data with small number of patients show promising results with a complete response (100% dry) after only 1 week of training in 33–50% [12]. However, no large clinical randomized trials exist to evaluate its true additional effect in urotherapy.

### Aim and objective

The aim of this study is to investigate whether the SENS-U improves the cost-effectiveness of urotherapy. The objective is to find out the most effective urotherapy modality for children with functional daytime urinary incontinence (DUI). This paper describes the study design and the interventions of a parallel-group randomized trial. We hypothesize a steeper individual learning curve and more cost-effective training period if the SENS-U is added to urotherapy.

## Methods/design

### Study design and setting

This study is multicenter clinical superiority parallel-group randomized controlled trial, designed according to the SPIRIT 2013 checklist (Additional file 1). The final study protocol version 6.0, December 2021, was approved by the Ethics Committee of Arnhem-Nijmegen in the Netherlands (NL 78403.091.21) and registered in ISRCTN44345202 (March 2022).

Participating centers in the Netherlands are the Wilhelmina Children’s Hospital in Utrecht, the Radboudumc Amalia Children’s Hospital in Nijmegen, Isala Clinic in Zwolle, and TOP voor kinderen in Arnhem. The first two are academic referral centers, the latter peripheral centers. The study will be conducted from June 2021 to June 2025. First-, second-, and third-line centers are participating in this study with the intention to select not only therapy-resistant children referred to third-line centers but also children seeking medical attention for functional DUI at the start of their condition.

The study consist of three parallel arms: urotherapy (care as usual), urotherapy with addition of a SENS-U device, and urotherapy with addition of a SHAM device. Outcomes parameters are measured at baseline, after the end of 3-week training with or without SENS-U/SHAM, after 3 months at the end of urotherapy, and 6 months after start of the training. Total study duration is 4 years. Individual study duration for subjects is 6 months.

### Recruitment, inclusion procedure, eligibility criteria, and consent

Children between 6 and 16 years with functional DUI for at least 3 months (including ≥ one episode a month), in which urotherapy is considered a suitable treatment option, are recruited at the outpatient department of the participating centers. Children of all gender, ethnic, and socio-economic backgrounds are eligible. Referring general practitioners, pediatricians, and urotherapists—among other health care providers involved in treatment of LUTD in children—will be informed about the trial in journals, conferences, and using online media including a study web site. Children and/or parents who are not yet under active treatment but still interested in the trial can contact the research team by email. One of the research members will contact parent(s) and invite them to the outpatient department in one of the nearby participating centers. Candidates who fulfil all inclusion criteria will receive oral and written information about the study (Additional file 2). A subsequent appointment within 14 days is planned, to answer any remaining questions. If candidates are willing to participate and after signed informed consent, they are allocated to one of the three study arms and planned for intake and start of their urotherapy.

The exclusion criteria are :History of congenital urogenital anomalies except for successfully treated mild infravesical obstruction (meatal stenosis, mild urethral valves) > 3 months before inclusionHistory of neurological underlying disease as the cause of LUTDHistory of Botox treatment for LUTD < 3 months for inclusionRecurrent urinary tract infection at the start of the studyUntreated or treated but persisting functional constipation according to Rome IV criteria at the start of the study < 6 months before inclusionRecurrent culture proven UTI (less than 3 months before start of the study or not under control by prophylactic antibiotics)Previous urotherapy/bladder training within 6 months of start of the studyObesity preventing accurate measurement by the SENS-U as defined as a BMI > 95th percentile according to age/genderSkin problems in the suprapubic area that are incompatible with the SENS-U adhesiveDevelopmental and intellectual disabilities or severe behavioral and social problems that are incompatible with protocolled urotherapy treatment based on the history and opinion of the clinician/urotherapist

### Urotherapy/bladder training

All subjects will receive urotherapy which starts with explanation and instructions. These instructions are also handed out in paper. At baseline, uroflowmetry and ultrasound to measure post void residual (PVR) is performed at least twice. Several patient-related outcome measurements (PROMS) are collected: a 48-h frequency voiding chart (FVC), questionnaires (Pediatric Incontinence Quality of Life (PINQ), EQ-5D-Y), and Rome IV criteria. Number and severity of wet days per week is assessed as baseline parameter.

After this, urotherapy is given for 12 consecutive weeks according to ICCS standards [6]. During this practice period, counseling is given at frequent follow-up appointments according to the local protocol in each center (at least two contact moments after intake and before follow-up at 3 months). Medication for constipation, prophylactic antibiotics, or medication to suppress bladder overactivity are continued if applicable. After 3 months of training, the urotherapist evaluates the outcome of training and number and severity of urinary incontinence per week is assessed again. Uroflowmetry and ultrasound for PVR and voiding diary/FVC parameters are collected again, and outcomes are discussed with the child and its parents. Questionnaires (PINQ, EQ-5D-Y) are filled in, and Rome IV criteria are determined.

If continence is not achieved (or not sufficiently) after 3 months, alternative treatments are discussed. Another contact moment is planned 6 months after start of the treatment to re-evaluate the status, assess the number and severity of urinary incontinence, and collection of previous mentioned PROMS. This is the end of the study period for participating subjects.

### Interventions for subjects randomized to urotherapy + SENS-U or urotherapy + SHAM

Urotherapy is given as mentioned previously and the same for all participating subjects, including the PROMS. In addition the SENS-U or SHAM is added. A health care provider will administer and install the device and explain parents and child how to apply and use the device. The SENS-U is used to provide biofeedback which teaches the child the feeling that corresponds with the feeling of a full bladder. The alarm can be personalized by adjusting the percentage of bladder filling at which it sends an alarm, based on the child’s own bladder capacity and FVC. The SENS-U is able to monitor the natural bladder filling during regular activity in children, as required for application in urotherapy.

The feeling of a device on the children’s belly could increase awareness of their bladder and might induce a placebo effect. Therefore, we included a placebo group, wearing a SHAM device that alerts independent of bladder filling at a set interval. The SHAM device resembles the traditional timer watch which is currently often used in urotherapy [13]. Therefore, it is not considered an extra burden for children to wear a SHAM device. The SHAM and accompanying instructions for use are identical to the SENS-U. The interval between alarms is randomly chosen between 2 and 3 h to appear realistic. To establish a good learning effect but preventing any dependency of the child on a device, either the SENS-U or SHAM will be worn for a total of 21 consecutive days in the overall 3 months of training. After the period of 21 days, an evaluation is done addressing items like comfort and user friendliness. Before the start of the study, all involved health care professionals are instructed about the use of the SENS-U/ SHAM. The project leader will coordinate instructions and training on the research protocol for the SENS-U study. An overview of the study procedures are shown in Table 1.

**Table 1 Tab1:**
[figure not shown]
Overview of study procedures

### Randomization

Subjects are randomized to urotherapy for 3 consecutive months with or without 3 weeks use of SENS-U/SHAM device. Permuted block randomization with block size 6 stratified for age groups (6–7 years, 8–10 years, 11–15 years) will be done within each participating center by a computer. The program used is CASTOR EDC. Because some heterogeneity of urotherapy within the participating centers exists (in mode and interval of guidance by the urotherapist), the randomization will be performed within each center to correct for small differences between centers. Subjects are blinded for SENS-U versus SHAM device condition. An independent research member (other than the actual urotherapist treating the subject) is performing the randomization, assigns the device number (either SENS-U/SHAM) to the subject, plans the intake, and administers the device. This is done so outcomes can be attributed to the intervention itself and are only minimally influenced by behavior of the urotherapist who guides the training. The training period is 3 months with use of a device for 3 weeks if randomized to SHAM/ SENS-U during that period. Necessary unblinding during the period of device use (3 weeks) due to urgent medical reasons or unexpected serious adverse advents is very unlikely.

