This study has several strengths. Children from first-, second-, and third-line centers throughout several areas in the Netherlands are included to represent the overall group of children with functional DUI as much as possible. It is one of the few studies that will give a better insight in adherence of alarm systems used, as current literature concerning this element is sparse. As previously mentioned, trials studying not only the effect but also the cost-effectiveness of certain treatment modalities are essential as overall health costs are increasing. The study also has some potential limitations. Complete blinding of subjects is only possible for those allocated to either a SENS-U or SHAM device. Those allocated to urotherapy alone are not blinded (nor is the urotherapist in this case). As cognitive behavioral treatment is an important part of training, motivation in those not randomized to any type of device might be impaired. Potential discomfort or social embarrassment in those allocated to a SENS-U or SHAM might lead to less adherence and subsequent impact on outcome as well.

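### A fixed, published block size of 6 with an open usual-care arm leaves comparisons with usual care open to selection at enrolment; the upper age boundary also needs one line of clarification.

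*Protocol article*

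**What the plan says.** The Randomization section states "Permuted block randomization with block size 6 stratified for age groups (6–7 years, 8–10 years, 11–15 years") and adds that this "will be done within each participating center by a computer". The abstract gives the rest of the structure: "Four centers, two academic hospitals, and two general care (peripheral) centers are participating", and "Participants will be randomized at a 1:1:1 ratio into three groups".

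On blinding, the Randomization section says "Subjects are blinded for SENS-U versus SHAM device condition", while the Discussion concedes "Those allocated to urotherapy alone are not blinded (nor is the urotherapist in this case").

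On who allocates, the Randomization section says "An independent research member (other than the actual urotherapist treating the subject) is performing the randomization, assigns the device number", plans the intake and administers the device. The stated purpose is to limit the urotherapist's influence on outcomes. The recruitment section places allocation after signed consent. It also has a member of the research team contact and invite families who approach the trial themselves.

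On age, the recruitment section admits "Children between 6 and 16 years with functional DUI for at least 3 months".

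**The concern.** When the block size is constant and known, each allocation that becomes visible narrows what is left in the block. Once both control places are used, every remaining child in that block will get a device. Once all four device places are used, every remaining child will be a control. If a person who influences whether or when a family enrols can follow that sequence, families could be matched to a slot.

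The Discussion itself names a reason to care, since it expects that children given no device may be less motivated. The data analysis section adjusts for baseline, centre, age, antimuscarinic dose and adherence or drop-out. None of these is the family's motivation before allocation, so selection on it would not be removed. The comparisons at stake are SHAM versus control, which is the named measure of the placebo effect, and any other comparison with usual care, including the three-group mixed model.

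The second, smaller matter is that the eligibility wording reaches 16 years while the oldest stratum is labelled 11–15 years.

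**Working it through.** The article gives no figure for predictability, so there is none to reproduce.

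**Inputs**
- Block size 6 and three age groups: Randomization section.
- Four centres, ratio 1:1:1: abstract.
- Total of 480 children: Sample size section.
- Control status visible after allocation, device type masked: Discussion and Randomization sections.

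**Block content.** 6 places at 1:1:1 give c = 2 control and d = 4 device places (2 SENS-U, 2 SHAM). There are 6!/(2!·4!) = 15 equally likely control/device orders.

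**Allocations certain in advance.** A place is certain when all places from it to the end of the block are of one kind. The expected number is the mean length of the closing run:
- certain device: d/(c+1) = 4/3 per block, and (4/3)/6 = 22.2% of allocations
- certain control: c/(d+1) = 2/5 per block, and (2/5)/6 = 6.7%
- together: 26/15 = 1.733 of 6 = 28.9%

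By place in the block:

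| Place | Probability certain |
|---|---|
| 1 | 0 |
| 2 | 0 |
| 3 | 1/15 = 6.7% |
| 4 | 3/15 = 20.0% |
| 5 | 7/15 = 46.7% |
| 6 | 100% |

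The sum is (1 + 3 + 7 + 15)/15 = 26/15, which agrees.

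**Best guess.** At each place the observer guesses the kind with more places left. The probabilities of being right are 2/3, 2/3, 2/3, 11/15, 11/15 and 1. Their mean is (2 + 22/15 + 1)/6 = 67/90 = 74.4%. Always guessing device is right 4/6 = 66.7% of the time, so following the sequence gains about 8 percentage points.

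**Incomplete last blocks.** There are 4 × 3 = 12 strata, on average 480/12 = 40 children each. Equal size is an assumption. Forty children fill 6 blocks and 4 places of a seventh. The share certain is then (6 × 26/15 + 4/15)/40 = 10.67/40 = 26.7%, slightly below 28.9%.

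**Alternatives.** For a fixed, known block the same formula gives 44.4% (size 3), 21.4% (size 9) and 17.0% (size 12). For randomly mixed sizes, assume they are equally likely and that the observer knows where each block starts but not its size. Enumeration then gives:
- 3 and 6: 19.3%
- 6 and 9: 12.9%
- 3, 6 and 9: 10.7%

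**Age.** In completed years, the groups 6–7, 8–10 and 11–15 cover every child from the 6th to the 16th birthday. A child who has turned 16 is covered only if eligibility excludes that child, and the article does not say whether it does.

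**The case against.** Four objections have weight.

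1. **The primary comparison.** A reader might infer that the main result is at risk. The documents do not support that. Knowing that a device comes next does not reveal which device, and subjects are masked to it. This objection stands in full.

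2. **The size of the figure.** A reader might take 29% as the share of allocations recruiters will know. It is a ceiling for one person who knows the block size and the block starts, has seen every earlier allocation in that list, and can influence enrolment. Most of it (22.2 of 28.9 points) is certainty of device, which is the likelier guess anyway. This stands, and the figure should be read that way.

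3. **Existing safeguards.** Allocation is by computer, after consent, by someone other than the treating urotherapist. Nothing says that recruiters follow the sequence. These features lower the risk but do not exclude it. Independence is defined only against the treating urotherapist, and the article does not separate the people who invite and consent families from the person who randomises and therefore sees the sequence. One exclusion criterion also rests on the opinion of the clinician or urotherapist, and the urotherapist is the role the Discussion describes as unblinded for controls. The full protocol, which is not shown, may separate these roles; the article's fixed and published block size is the same either way.

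4. **Age.** A reader might infer that an eligible 16-year-old cannot be allocated or would be put in the wrong stratum. Up to the 16th birthday is an ordinary reading of the eligibility wording, and the strata cover that range completely. No failure is shown; only the boundary is unclear.

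**Conclusion.** The point holds as a limited design weakness. One fixed, published block size within each centre and age group, combined with an open usual-care arm, makes up to 28.9% of control-or-device allocations certain in advance (about 26.7% if strata hold 40 children each). It raises the best guess from 67% to 74%. This assumes an observer who knows the block starts and has followed the whole list. It measures opportunity, and nothing in the article shows that steering has occurred or how large any bias would be.

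The exposure is confined to comparisons with usual care, notably the placebo-effect estimate from SHAM versus control. The primary SENS-U versus SHAM comparison is not exposed as long as device type stays masked. The age wording is a boundary ambiguity that needs reconciling and carries no shown consequence.

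**What to change.** For blocks not yet opened, have the randomisation program draw block sizes at random from multiples of 3, for example 3, 6 and 9, and do not disclose the sizes to sites. Under the assumptions above this lowers the certain share from 28.9% to 10.7%. Non-disclosure and mixing are both essential, since a known fixed block of 3 would be worse (44.4%). In addition, state that those who recruit and consent families do not see the allocation sequence of their stratum, and that the person who randomises does not recruit.

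The cost is a program setting and a short amendment. The downside is slightly larger possible imbalance: within an open block, two arms can differ by at most 2 children with size 6 and by at most 3 with size 9.

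Separately, add one line reconciling the upper age limit in the eligibility criteria with the label of the oldest stratum, and use the same boundary in the randomisation program and the analysis.
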